### Potential adverse effects of bicarbonate therapy

Bicarbonate is awkward to take, as tablets are large, and multiple tablets usually need to be taken. Sodium bicarbonate contains 6 mmol of sodium per 500 mg, which could lead to increased blood pressure (50 mmol of sodium per day has been projected to increase systolic blood pressure by 3.6 to 5.6 mmHg) [15] and fluid overload. Observational studies suggest that higher serum bicarbonate is associated with an increased risk of heart failure in patients with CKD [16]. There is also a possible effect on vascular calcification [7]; raising the blood pH may make calcium and phosphate less soluble, thus promoting precipitation of calcium phosphate within vessel walls. Abdominal discomfort and bloating are recognized side effects listed in the British National Formulary (BNF), perhaps via generation of carbon dioxide in the gut.

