### Intervention

The study medication will be administered as oral tablets. Placebo and active tablets will be identical in appearance. Bicarbonate tablets will contain 500 mg of sodium bicarbonate (6 mmol sodium and 6 mmol bicarbonate); placebo tablets will be composed of lactose. The Good Medical Practice (GMP)-compliant investigational medicinal product manufacturer (Legosan AB, Kumla, Sweden) will prepare and bottle matching active and placebo tablets for the trial. Participants will commence therapy at a dose of 500 mg of oral sodium bicarbonate or placebo three times per day; reflecting a common starting dose in clinical practice. At 3 months, if serum bicarbonate is found to be <22 mmol/L, the dose will be increased to 1 g three times per day or placebo. This is equivalent to six tablets per day; larger doses are likely to worsen adherence to therapy. This dose is higher (3 g versus 1.8 g) than that used in a previous small RCT [13]; it is therefore likely to produce a larger increment in bicarbonate at an earlier time point, thus enhancing the ability of our trial to demonstrate beneficial effects on outcome parameters.

Randomisation will be via a centrally controlled web-based Good Clinical Practice (GCP)-compliant randomisation system, run by Tayside Clinical Trials Unit (TCTU). Investigators at each site will access the web-based system to allocate each participant at the end of the baseline visit. Randomisation will be stratified by site. To ensure balanced assignment across critical variables, a minimisation algorithm will be employed, using baseline age, sex and GFR category to balance allocation across trial arms.

To ensure that medication adherence is maximised, we will employ a combination of written information about the study medication and why taking it is important, together with aide memoirs including BiCARB-branded mugs and fridge magnets. In the second year of follow-up, regular telephone contact (at 15 and 21 months) will be made to remind participants about the importance of medication adherence. Interventions incorporating these components have been shown in a previous Cochrane review to enhance adherence [26]. If the study drug needs to be stopped or the patient wishes to stop they can remain in the study in order to perform an intention-to treat-analysis.

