### Outcomes

The primary outcome for the trial is the between-group difference in change for the Short Physical Performance Battery (SPPB) between baseline and 12 months. The SPPB is a validated measure of lower limb function that reflects everyday activity. It is a powerful predictor of subsequent disability, institutionalisation and death in older people [27–29], and has more data validating its use in older people than any other measure of physical function. Secondary outcomes will include SPPB at other time points, along with measures of physical function (grip strength as measure of upper limb function, and six minute walk as a measure of endurance capacity), quality of life (generic, measured using the EQ-5D tool, and disease-specific, measured using the KDQoL tool [30]), anthropometry, renal function and bicarbonate concentrations, markers of bone turnover, calcium and phosphate metabolism, blood pressure and B-type natriuretic peptide. Key outcomes are listed in Table 2.

**Table 2 Tab2:** Outcome measures and measurement points

OUTCOME	TIMELINE						
	Screening	Baseline	3 months	6 months	12 months	18 months	24 months
*Informed Consent*	X						
*Inclusion/Exclusion Criteria*	X						
*Medical History/Demographics*	X						
*Adverse Events Recorded*		X	X	X	X	X	X
*Physical function measures*							
Short Physical Performance Battery		X	X	X	X		X
Hand Grip Strength		X	X	X	X		X
Six Minute Walk Test		X	X	X	X		X
*Blood measures*							
Sodium	X	X	X	X	X		X
Potassium	X	X	X	X	X		X
Creatinine	X	X	X	X	X		X
Urea	X	X	X	X	X		X
Bicarbonate	X	X	X	X	X		X
Estimated GFR	X	X	X	X	X		X
Calcium		X	X	X	X		X
Phosphate		X	X	X	X		X
Alkaline phosphatase		X	X	X	X		X
Magnesium		X	X	X	X		X
Albumin		X	X	X	X		X
Haemoglobin		X	X	X	X		X
Thyroid function		X	X	X	X		X
HbA1c		X	X	X	X		X
Total Cholesterol		X	X	X	X		X
Cystatin C		X	X	X	X		X
Study Biobank Samples		X	X	X	X		X
*Urine Sample*							
Protein/creatinine ratio		X	X	X	X		X
Albumin/creatinine ratio		X	X	X	X		X
*Questionnaires*							
EQ-5D		X	X	X	X		X
KDQoL		X	X	X	X		X
Health Diary		X	X	X	X		X
Falls Diary		X^a^	X	X	X	X	X
*Anthropometric Measurements*							
Mid-arm Circumference		X	X	X	X		X
Triceps Skin Fold Thickness		X	X	X	X		X
Mid-thigh Circumference		X	X	X	X		X
Height		X					
Weight		X	X	X	X		X
*Vascular measures*							
Blood pressure and pulse	X	X	X	X	X		X
B-type natriuretic peptide		X			X		X
*Bone and calcium metabolism*							
Calcium		X	X	X	X		X
Phosphate		X	X	X	X		X
Parathyroid hormone		X			X		X

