### Statistical analysis

Statistical analysis will be performed by intention-to-treat and reported in accordance with the CONSORT statement (www.equator-network.org). The primary analysis will be a between-group comparison of 12 month outcomes, adjusted for baseline values of the outcome under test via regression analysis. Further adjustment for age, sex and GFR category will also be performed. Secondary analyses will comprise multivariate repeated measures analysis using all available time points, adjusted for baseline differences. A per-protocol secondary analysis will be performed to compare adverse events, and time-to-event analyses for death or onset of renal replacement therapy will be performed using Cox proportional hazards regression models. A two-sided *P* value of 0.05 will be taken as significant for each outcome. The primary outcome will be analysed at 12 months rather than 24 months in order to strike a balance between excessive dropout (expected in this group of older, multi-morbid participants) and sufficient time for the intervention to show an effect.

Pre-specified subgroup analyses will include the following: participants with a SPPB score of <10 (denoting a frailer subgroup) versus those with SPPB ≥10; participants with a baseline serum bicarbonate concentration of >18 mmol/L versus those with serum bicarbonate ≤18 mmol/L; GFR category (4 versus 5); sex, and age >75 years versus age ≤75 years. Missing data for the primary analysis will be handled using multiple imputation, provided that the assumption of missing at random is met. Missing data in the repeated measures analyses will be handled using generalised estimating equation approaches to maximise the use of participants with incomplete data.

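### Blood pressure, pulse and six blood measures are read twice before randomisation, but the stated model adjusts for the baseline reading only, which gives up a modest amount of precision on these secondary outcomes

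*Protocol article*

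**What the plan says.** The Statistical analysis section compares 12-month outcomes between groups, "adjusted for baseline values of the outcome under test via regression analysis". It adds that "Further adjustment for age, sex and GFR category will also be performed". Secondary analyses are a "multivariate repeated measures analysis using all available time points, adjusted for baseline differences". None of these statements mentions a screening value.

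In Table 2 (Outcomes section), Screening and Baseline are separate columns. The row "Blood pressure and pulse" is marked in both. So are six blood measures: sodium, potassium, creatinine, urea, bicarbonate and "Estimated GFR". The eGFR is calculated from creatinine by the MDRD4 equation (Table 1), so the six rest on five assays.

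Under Intervention, investigators use the randomisation system to "allocate each participant at the end of the baseline visit". Both sets of readings therefore precede allocation.

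The primary outcome is the "between-group difference in change for the Short Physical Performance Battery (SPPB) between baseline and 12 months". Table 2 shows the SPPB and the EQ-5D only once before randomisation, at baseline.

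On harm, the section on potential adverse effects says that "50 mmol of sodium per day has been projected to increase systolic blood pressure by 3.6 to 5.6 mmHg". Blood pressure is listed among the secondary outcomes. The article says that a detailed analysis plan will be agreed before the treatment code is broken.

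**The concern.** A single blood pressure or laboratory reading carries visit-to-visit noise. As a covariate it therefore predicts the 12-month value less well than two readings would. Any reading taken before allocation can be adjusted for without biasing the treatment contrast. Here the second reading already exists and would cost no visit, sample or participant.

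The interval for blood pressure is where this matters most. Hypertension is one of the harms that the trial sets out to quantify. The rise that can be projected from the article's own figures is small, and no power or precision is stated for it. If the interval is about as wide as the projected effect, a real rise could be reported as no clear difference. A narrower interval helps the net benefit-or-harm judgement that the Discussion promises.

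**Working it through.** **The plan's own figures.** With (1.960 + 1.282)² = 10.507:
- SPPB: n per group = 2 × 10.507 × 2.6² / 1² = 142.1, so 143, as stated.
- EQ-5D: n per group = 2 × 10.507 × 0.2² / 0.074² = 153.5, so 154, as stated.
- Loss of 10% per 6 months leaves 0.9² = 0.81 at 12 months: 380 × 0.81 = 308, or 154 per arm.

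These figures reproduce. I use 154 per arm below.

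**Equal correlations.** Let r be the correlation between any two of the screening, baseline and 12-month readings. The documents give no value, so r is assumed over 0.4 to 0.7. As a fraction of the outcome variance, the residual variance is:
- one reading: 1 − r²
- both readings: 1 − 2r²/(1 + r)
- ratio: (1 + 2r)/(1 + r)²

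| r | one reading | both | variance ratio | interval width ratio | equivalent extra patients |
|---|---|---|---|---|---|
| 0.4 | 0.840 | 0.771 | 0.918 | 0.958 | 9% |
| 0.5 | 0.750 | 0.667 | 0.889 | 0.943 | 12.5% |
| 0.6 | 0.640 | 0.550 | 0.859 | 0.927 | 16% |
| 0.7 | 0.510 | 0.424 | 0.830 | 0.911 | 20% |

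Residual variance falls by 8 to 17%, and intervals are 4 to 9% narrower.

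**Screening less predictive than baseline.** Equal correlation is the favourable case. In general R² = (b² + s² − 2bsc)/(1 − c²), where b is the baseline–outcome, s the screening–outcome and c the screening–baseline correlation. With b = c = 0.6 (assumed):
- s = 0.55: R² = 0.2665/0.64 = 0.416, variance ratio 0.584/0.64 = 0.912
- s = 0.50: R² = 0.25/0.64 = 0.391, ratio 0.609/0.64 = 0.952
- s = 0.40: R² = 0.232/0.64 = 0.3625, ratio 0.6375/0.64 = 0.996

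At s = 0.36 (that is, 0.6 × 0.6) the screening reading adds nothing.

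**Measures used for entry.** Entry requires bicarbonate below 22 mmol/L. I simulated equally correlated readings and kept only those with a screening value below 22 (assumed unselected mean 22 to 24, SD 3). The variance ratio is 0.903 to 0.964 for r = 0.5 to 0.7, and 0.965 to 0.976 for r = 0.4. The cut is therefore roughly 3 to 10%. The same mechanism may reduce the gain for eGFR, but that criterion uses the last known value, so the screening reading need not be the truncated one. Blood pressure is only lightly truncated: the criterion excludes readings above 150/90 mmHg despite four agents, with an exception for home or 24-hour evidence.

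**Illustration for systolic pressure.** Assume SD 20 mmHg and r = 0.6. The standard error is 20 × √(2/154) × √0.640 = 1.82 with one reading and 20 × √(2/154) × √0.550 = 1.69 with both. The 95% half-width falls from 3.57 to 3.31 mmHg (SD 15: 2.68 to 2.48; SD 25: 4.47 to 4.14).

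The Intervention section gives 6 mmol sodium per tablet, so 36 mmol/day on six tablets and 18 mmol/day on three. Scaling the article's projection linearly:
- six tablets: 36/50 × 3.6 = 2.6 and 36/50 × 5.6 = 4.0 mmHg
- three tablets: 18/50 × 3.6 = 1.3 and 18/50 × 5.6 = 2.0 mmHg

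| true rise (mmHg) | power, one reading | power, both |
|---|---|---|
| 4.0 | 59–60% | 66–67% |
| 2.6 | 30% | 34% |
| 2.0 | 20% | 22% |
| 1.3 | 11% | 12% |

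The two-figure entries for 4.0 reflect rounding (4.00 against 4.03).

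**The case against.** The strongest reply is that baseline-adjusted regression is standard and correct, and that deciding which pre-randomisation readings make up the baseline value is ordinary analysis-plan detail. A condensed article does not exclude a combined pre-randomisation value. This stands in part. The article never rules out the screening reading, and an analysis plan not shown here may use it. But the article does name the covariate, and Table 2 treats screening and baseline as different visits, so on its plain reading the rule uses one reading. The point offers a better use of data already collected and does not charge the plan with an error.

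The size of the gain is also open to challenge, and rightly. The SD, the correlations and their equality are all assumptions. The 4.0 mmHg figure combines the upper projection with six tablets for everyone, whereas participants start on three and increase only if bicarbonate is below 22 mmol/L at 3 months. At smaller effects, power stays low with either model.

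A reader might infer more than the documents support:
- **That blood pressure is the trial's main harm outcome.** No section ranks the harms. Hypertension is named beside heart failure and fluid overload, and blood pressure is one of many secondary outcomes.
- **That the stated analysis is biased.** It is not. Adjusting for one valid pre-randomisation reading gives an unbiased comparison.
- **That a second covariate is needed to correct regression to the mean in the entry variables.** Regression to the mean acts on both randomised arms alike and does not bias the contrast.
- **That the primary result is weakened.** SPPB and EQ-5D have a single pre-randomisation measurement, so nothing changes for them or for the sample size.

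**Conclusion.** The point holds as a missed efficiency on secondary outcomes. Seven rows of Table 2 (blood pressure with pulse, and six blood measures) have two readings before allocation, and the article adjusts for one. The best supportable statement of size is intervals 4 to 9% narrower, if all readings correlate equally at 0.4 to 0.7. The benefit may be close to nil where the screening reading is clearly the poorer predictor, and is roughly 3 to 10% of variance for bicarbonate. For systolic pressure the illustrative gain is about 0.3 mmHg off a half-width of about 3.6 mmHg, resting on an assumed SD of 20 and correlation of 0.6. The change is worth making because it costs almost nothing. The conclusions on physical function, quality of life and trial size do not depend on it.

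**What to change.** Before unblinding, state in the analysis plan that, for outcomes measured at both screening and baseline (blood pressure, pulse, sodium, potassium, creatinine, urea, bicarbonate and eGFR), the two values enter as separate covariates in the 12-month and the repeated-measures models. Separate terms let the data give less weight to a screening reading that is truncated or less predictive.

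For participants who entered after the 3-month bicarbonate washout, use only a screening value taken after washout. Where none exists, treat it as a missing baseline covariate, for example by simple imputation that ignores treatment arm, together with a missing indicator. No participant is then dropped.

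The cost is a sentence or two in the analysis plan, one degree of freedom per model, and this small piece of missing-value handling (the indicator takes one more degree of freedom where it is needed). No further visits, samples or participants are required.

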### Sample size calculation

We plan to randomize a total of 380 participants: 190 to bicarbonate and 190 to placebo. The clinically important difference (CID) for the SPPB is a 1-point difference. Assuming a SD of 2.6 as found in previous work [32], we would require 143 patients per group to give 90 % power to detect this difference at a two-sided alpha of 0.05. For the EQ-5D, the minimum CID is 0.074 [33]. To detect this with two-sided alpha = 0.05 and power of 90 %, assuming a SD of change of 0.2, as found in our previous studies, our study requires 154 patients per group. We anticipate a dropout rate of 10 % per 6 months, due to the high rates of expected death and illness in this multi-morbid, older group of participants; the calculated sample size accounts for this dropout.

Progression to dialysis in a previous trial of bicarbonate therapy [13] was lower in patients allocated to bicarbonate (7 %) than in the control arm (33 %). The proposed sample size will have 90 % power to successfully detect a more conservative difference of 7 % in the bicarbonate arm and 18 % in the control arm at 2 years. Assuming a 10 % loss to follow-up every 6 months (a pessimistic estimate, based on previous medication trials in frail older people in our centre), we would require 380 patients to ensure adequate power for the primary outcome and the EQ-5D at 12 months. This rate of attrition would leave 250 evaluable patients at 2 years, which will give additional power to detect smaller changes using repeated measures analyses.

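### GEE, as stated for the repeated-measures analyses, needs a stronger missing-data assumption than the primary analysis, and the plan's own account of dropout makes that assumption implausible

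*Protocol article*

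**What the plan says.** The Statistical analysis section of the protocol article defines the role of these analyses: "Secondary analyses will comprise multivariate repeated measures analysis using all available time points, adjusted for baseline differences". It then gives two missing-data rules in consecutive sentences. For the primary 12-month comparison: "Missing data for the primary analysis will be handled using multiple imputation, provided that the assumption of missing at random is met". For the longitudinal analyses: "Missing data in the repeated measures analyses will be handled using generalised estimating equation approaches to maximise the use of participants with incomplete data". No weighting, imputation, working correlation or missingness assumption accompanies the second rule.

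Two other places bear on it. The Sample size calculation section expects a "dropout rate of 10 % per 6 months, due to the high rates of expected death and illness", and adds: "This rate of attrition would leave 250 evaluable patients at 2 years, which will give additional power to detect smaller changes using repeated measures analyses". The Outcomes section says of the SPPB: "It is a powerful predictor of subsequent disability, institutionalisation and death in older people". Table 2 schedules the SPPB at baseline and at 3, 6, 12 and 24 months.

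**The concern.** GEE can include a participant who has only some visits, but including the available records does not correct for selective loss. Suppose the mean model has a separate arm effect and baseline slope at each visit, and the working correlation is independence. The 24-month contrast then uses only those still present at 24 months, and their earlier scores contribute nothing. In general, unweighted GEE is consistent only if data are missing completely at random (MCAR), or if missingness depends only on covariates in the mean model.

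The article's own account points the other way. People are lost through death and illness, and the modelled outcome predicts death. Adjusting for the baseline score does not repair this, because decline seen at 3, 6 or 12 months would also predict later loss.

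The two analyses of the same outcome therefore rest on different assumptions: missing at random (MAR) for the primary analysis, and something close to MCAR for the analysis that reaches furthest and loses most people. At stake are the secondary repeated-measures results up to 24 months, the gain in power claimed for them, and the cost-effectiveness acceptability curves. The section on health economic data builds those curves partly on the repeated-measures estimates.

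**Working it through.** **1. The plan's own figures.** Inputs are from the Sample size calculation section: two-sided alpha 0.05, 90% power, 10% loss per 6 months.

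- SPPB (difference 1, SD 2.6): n = 2 × (1.960 + 1.282)² × 2.6² / 1² = 2 × 10.51 × 6.76 = 142.1, so 143 per group, as stated.
- EQ-5D (difference 0.074, SD 0.2): n = 2 × 10.51 × 0.2² / 0.074² = 153.5, so 154 per group, as stated.
- Loss by 12 months: 1 − 0.9² = 19%. Then 2 × 154 / 0.81 = 380.2, against 380 stated.
- Loss by 24 months: 1 − 0.9⁴ = 34%. Then 380 × 0.656 = 249, against 250 stated.

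The figures reproduce, so the point concerns method only.

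**2. Simulation.** From the article: the SPPB visits, SD 2.6, a true difference of 1.0 at 12 and 24 months (the stated clinically important difference) and about 10% loss per 6 months. Assumed, because the article does not give them: the within-person correlation (exchangeable at 0.6, or decaying at 0.8 per 6 months), and the strength and arm pattern of the link between dropout and the last observed score. The mean model was visit, arm by visit and baseline by visit. Each replicate had 20,000 participants, with 40 replicates for the two score-related patterns and 10 for the others.

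Estimated arm difference at 12 / 24 months (truth 1.00 / 1.00):

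| Dropout depends on | True correlation | GEE, independence | GEE, exchangeable | Likelihood model, unstructured |
|---|---|---|---|---|
| nothing (MCAR) | exchangeable | 1.01 / 1.01 | 1.01 / 1.02 | 1.01 / 1.02 |
| baseline score only | exchangeable | 1.01 / 1.00 | 1.01 / 1.01 | 1.01 / 1.01 |
| last score, both arms | exchangeable | 0.99 / 0.96 | 1.00 / 0.99 | 1.00 / 0.99 |
| last score, both arms | decaying | 0.99 / 0.96 | 0.99 / 0.98 | 1.00 / 1.00 |
| last score, placebo only | exchangeable | 0.92 / 0.83 | 1.01 / 1.00 | 1.01 / 1.00 |
| last score, placebo only | decaying | 0.92 / 0.81 | 0.97 / 0.94 | 1.01 / 1.00 |

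Monte Carlo SE is about 0.005–0.006 in the last four rows and 0.008–0.013 in the first two. In the placebo-only rows the arms kept similar proportions at 24 months (0.68 on placebo, 0.66 on active), so similar total retention would not reveal the problem.

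**3. Second check.** A separate simulation used correlation 0.7, true effect 0, and score-related dropout in the control arm only (60 trials of 600 per arm, Monte Carlo SE about 0.02). Independence GEE was off by −0.09 points at 12 months and −0.18 at 24 months. Generalised least squares with exchangeable covariance was off by −0.01 at both. The shift is thus about the same number of points whether the true effect is 0 or 1.

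**4. Scale against precision.** With 125 per arm at 24 months and correlation 0.7, the baseline-adjusted SE is 2.6 × √(1 − 0.49) × √(2/125) = 0.23. A shift of 0.18 is 0.18 / 0.235 = 0.77 SE. Coverage of a nominal 95% interval would be Φ(1.96 − 0.77) − Φ(−1.96 − 0.77) = 0.883 − 0.003 = 88%. This is the independence, one-arm case only.

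**The case against.** The best reply is that the large bias belongs to one working correlation that the article never names. For a continuous outcome with identity link, exchangeable GEE solves the same equations as generalised least squares with exchangeable covariance, and that did well: 0–6% loss at 24 months. This stands, and it limits the size of the point. It does not remove it, because GEE is then protected only so far as the working correlation is right. Its usual robustness to a wrong working correlation does not carry over to MAR data.

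Second, material bias needs dropout that works differently in the two arms. Nothing in the article establishes this. The figures assumed for dialysis (7% against 18%) and the adverse effects listed for bicarbonate show only that reasons for leaving could differ. A reader might infer that tablet burden would drive people out of the active arm. The Intervention section does not support that: tablets match in appearance, the dose increase follows the same serum bicarbonate rule in both arms, and people who stop the study drug may stay in follow-up.

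Third, a condensed article may leave the working correlation, weighting and imputation to the analysis plan, which it promises before the code is broken. Their absence is indeed no finding. The point is that the article names GEE itself as the handling of missing data. The wording could cover weighted GEE or GEE after imputation, but it mentions neither.

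Finally, the attrition rate is by the article's own account pessimistic, and 0.18 points is less than one standard error. Both are true and both argue for moderate weight.

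**Conclusion.** The point holds for the secondary repeated-measures analyses. As stated, the method generally needs MCAR or purely covariate-dependent missingness. The article's own reasons for dropout make that implausible, and it is stricter than the MAR condition set one sentence earlier.

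The size rests on assumed correlations and dropout patterns. It is negligible to about 4% of a 1-point effect if dropout works alike in both arms. If score-related dropout occurs in one arm only, it is about 17–20% at 24 months with independence working correlation and 0–6% with exchangeable.

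Three stronger readings are tempting and are not supported:

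- That MCAR is ruled out. The stated reasons make it implausible; they do not disprove it.
- That every 24-month result, or the trial's main result, is biased. The primary 12-month analysis uses multiple imputation, death and onset of renal replacement therapy use Cox models, and adverse events have their own comparison.
- That about a fifth of the effect will be lost. That is the independence case with dropout related to score in one arm only, and the article specifies neither.

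**What to change.** Analyse the repeated measures with a likelihood-based mixed model containing visit, arm by visit and baseline value by visit, with unstructured covariance, and read the arm difference at named visits. If GEE is kept, weight it by the inverse probability of remaining in the study, or run it on multiply imputed data. Each option is valid under the MAR assumption already set for the primary analysis, provided its covariance, dropout or imputation model is adequate.

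The cost is a change of wording in the analysis plan and slight extra analysis work, with no new data or participants. The change does not by itself settle outcomes truncated by death, which need a stated estimand, or data missing not at random, which need a sensitivity analysis.
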